## Abstract

**Background:**

Personality disorders (PDs) are highly prevalent, impairing, and societally burdening conditions which can be treated effectively. Specialist psychotherapies are the first-choice treatment, but accessibility is hampered by implementation and sustainability issues. Manualised generalist treatments were designed as active control conditions to specialist psychotherapies in several effectiveness trials; their comparable performance led to them being regarded as more accessible alternatives to specialist psychotherapies. The Guideline-Informed Treatment for PDs (GIT-PD) is such a generalist treatment, which has shown promise and is broadly disseminated in the Netherlands and Belgium. However, there is an urgent need for controlled head-to-head comparisons of generalist and specialist treatments for PDs. Therefore, this study poses three main questions: 1) Is generalist treatment non-inferior compared to specialist treatment for severe PDs? 2) Is generalist treatment cost-effective compared to specialist treatment? 3) Which combination of patient characteristics predicts differential treatment outcomes between generalist and specialist treatments?

**Methods:**

P-DAET is a pragmatic multicentre randomised controlled non-inferiority trial. In total, 358 adult treatment-seeking participants with severe PDs will be included in five Dutch mental healthcare institutions. Participants are equally randomised to manualised generalist (GIT-PD) or specialist treatment (Mentalisation-Based Treatment/Schema Therapy). The primary outcome is improvement in personality functioning, assessed through assessor-blinded clinical interviews and supplemented with self-report questionnaires. Symptom severity and psychosocial functioning are important secondary outcomes. Participants complete assessments at 7 time-points: baseline (T0), 3 (T1), 6 (T2), 12 (T3), 18 (T4), 24 (T5), and 30 months (T6) after the start of treatment. The primary endpoint is at 18 months. An economic evaluation will be executed alongside the RCT. Differential treatment response based on candidate predictors at the patient level will be explored using a personalised advantage index (PAI).

**Discussion:**

P-DAET will determine the (cost-)effectiveness of generalist versus specialist treatment for severe PDs. This study will provide novel insights into the applicability of these treatments and their differential treatment response, enabling effective and personalised allocation of limited specialist treatment resources, while contributing to more accessible and good-enough care for individuals with severe PDs.

**Trial registration:**

ClinicalTrials.gov: NCT06789380. Retrospectively registered on February 5, 2025.

**Supplementary information:**

The online version contains supplementary material available at 10.1186/s12888-025-07550-4.

**Table Taba:** 

Administrative information	
Title {1a}	The effectiveness of generalist (GIT-PD) versus specialist treatment (MBT/ST) for severe personality disorders (Personality Disorders Access to Effective Treatment, P-DAET): study protocol of a pragmatic randomised controlled non-inferiority multicentre trial.
Protocol version {2}	Issue date: 27-Mar-2025 Protocol amendment number: 02 Authors: [name] **Revision chronology:** P-DAET Protocol 00, 2024-May-23 Original P-DAET Protocol 01, 2024-Aug-05 Amendment 01.: Primary reason for amendment: changes in sections 3, 8.1.2, 10.2, and 12.6 regarding additional time points, changes in secondary outcomes, and an increase in monetary compensation. Additional changes (these changes in and of themselves would not justify a protocol amendment): supplying the correct version of the C-SSRS. P-DAET Protocol 02, 2025-Mar-27 Amendment 02.: Primary reason for amendment: changes in sections 2, 3, 8.1.1, 8.1.2, 8.2, 8.3, 10.1, 10.2, and 11.2 regarding statistical analysis of primary and secondary outcomes, permission to collect informed consent digitally, and specification of the randomisation procedure. Additional changes (these changes in and of themselves would not justify a protocol amendment): changes on the title page and in section 12.1 regarding changes in personnel at Altrecht, and provided the name of the clinical data management platform used.

Composition of the coordinating centre and trial steering committee {3d}	A trial steering committee (TSC) consists of the principal investigator, a senior researcher per participating institution, two junior researchers, and site coordinators per participating site. The TSC has monthly meetings to discuss trial conduct, participant recruitment and inclusion, (serious) adverse events (SAEs), and publication of trial results. Furthermore, part of the senior researchers simultaneously act as (PhD) supervisor for the junior researchers, who are responsible for the day-to-day execution of the trial and oversee research assistants. This smaller core team meets on a weekly basis. Key roles external to the TSC and the executive core team consist of the data manager, advisors on statistical analysis and methodology, and the independent experts whom participants can turn to for impartial advice.
Open science	
Trial registration {4}	ClinicalTrials.gov: NCT06789380 Retrospectively registered on February 5, 2025.
Protocol and statistical analysis plan {5}	The planned procedures and the statistical analysis plan are available in the current publication, as well as in part within the time-stamped protocol approved by the accredited medical ethical research commission (METC Brabant), accessible on Clinical Trials.gov. The dissemination of amendments is detailed under Protocol amendments {31}.
Dissemination policy {8}	In general, all results will be published in peer-reviewed national and international journals. In addition, all publications will be disseminated to the public through national and international presentations and lectures, as well as the websites and newsletters of participating institutes (Altrecht, Dimence Groep, GGZ Oost Brabant, Arkin NPI, and GGZ de Viersprong), and the dedicated P-DAET-trial website. Further dissemination of results to participants of the study will be discussed with patient boards. Depending on the interpretation of the results, this study may lead to modifications of the regular mental health practice at the participating institutes and beyond.

**Note**: The numbers in curly brackets in this protocol refer to SPIRIT 2025 checklist item numbers (Chan et al. 2025).

## Introduction

### Background and rationale {9a}

Personality disorders (PDs) represent a significant health concern worldwide, estimated to affect around one in ten individuals in the general population [1, 2], with substantially higher prevalence rates observed in psychiatric samples [3]. PDs are associated with severely impaired quality of life [4], co-occurring somatic diseases [5], diminished labour productivity, and increased healthcare costs. More specifically, societal costs of PDs are comparable to schizophrenia and significantly exceed those of depression, anxiety disorders, multiple sclerosis, and epilepsy [6–8]. Therefore, access to effective treatment programs is highly relevant to both individual patients and society as a whole.

International guidelines recommend specialist psychotherapy as the first-choice treatment for PDs [9], with substantial evidence supporting the use of Dialectical Behaviour Therapy (DBT), Mentalisation-Based Treatment (MBT), Schema Therapy (ST), and Transference Focused Psychotherapy (TFP) for borderline PD (BPD) [10–14]. These specialist psychotherapies have consistently and reliably outperformed treatment as usual (TAU), with no evidence for superiority of one over another [10–15]. Recent applications of these evidence-based therapies have also shown effectiveness in treating other personality disorders, such as antisocial, paranoid, narcissistic, and cluster-C PD [16–19].

However, the implementation and long-term sustainability of these specialist treatments in routine clinical practice face various challenges. Apart from overall constraints in healthcare financing and limited organisational funding [20], key challenges are high staff turnover [21] and a shortage of trained therapists for specialist programs [22]. In addition, these programs are often relatively costly due to intensive training requirements for clinicians, high treatment dosage, and extended duration. Following implementation, the long-term viability of specialist programs needs sustained organisational support, time allocation, and competent team leadership, all of which are not always available [23, 24]. Consequently, the availability of evidence-based specialist treatments remains inadequate to meet the demand for treatment of individuals with PDs [22].

A second generation of clinical trials may have fortuitously revealed a potentially more accessible alternative to specialist treatment. After the first generation of trials had demonstrated that borderline PD could, in fact, be treated effectively, subsequent trials failed to establish superiority of any one specialist treatment, despite adhering to fundamentally disparate models. To ensure methodological rigour and avoid withholding active treatment from trial participants, a new series of clinical trials was conducted with an enhanced manualised active control condition [25]. As a result, manualised generalist treatments for personality disorders, such as General Psychiatric Management (GPM), Structured Clinical Management (SCM), Good Clinical Care (GCC), and Supportive Therapy, were introduced in a handful of trials evaluating specialist treatments, like DBT, MBT, Cognitive Analytic Therapy (CAT), and TFP [26–29]. Unexpectedly, the specialist treatments did not outperform the generalist treatments. These findings were reinforced by meta-analyses indicating that manualised generalist treatments can be as effective as specialist therapies, with both demonstrating superior outcomes compared to TAU [10, 11]. Given the high prevalence of individuals with PDs seeking care and the limited availability of specialist psychotherapies, generalist treatments were therefore reconsidered as viable, accessible alternatives to specialist treatments [22, 25]. The issue is, however, not without controversy, as a recent network meta-analysis by Setkowski et al. [12] did not corroborate earlier meta-analyses.

More specifically, the generalist treatments incorporated the common non-specific factors found in specialist treatments, referring to a structured treatment framework, an active and supportive therapist stance, the utilisation of interventions aimed at explorative clarification, change encouragement, and empathic validation, as well as a focus on affect and the therapeutic relationship [30]. At the same time, generalist models address barriers associated with specialist treatments through their shorter duration, lower treatment intensity, reduced costs, reliance on less specialised therapists, and fewer demands for training and supervision [25]. These features could make generalist treatments far more scalable and cost-effective than specialist therapies [22]. Although some research has yielded tentatively promising results, few trials have been conducted directly comparing the two treatment conditions [10–12]. Furthermore, all previous trials were designed to examine superiority. As a result, to unambiguously conclude that generalist treatments represent a valuable alternative to specialist treatments for PD trials that demonstrate non-inferiority need to be conducted.

The Guideline-Informed Treatment for Personality Disorders (GIT-PD) offers an evidence-informed treatment framework, comparable to GPM and SCM. GIT-PD was developed in the Netherlands to enhance access to mental health care for individuals with PDs [31]. Hutsebaut et al. [31] describe GIT-PD as a principle-driven model designed to optimise common factors and effective treatment components, in a structured manner across four levels of implementation: The institution, the clinical pathway, the treatment team, and the individual therapist. Moreover, GIT-PD offers flexibility, allowing it to adapt to the specific clinical needs of individuals with PDs and the existing competencies of professionals. Compared to specialist treatments for PDs, GIT-PD is characterised by lower treatment intensity, shorter duration, reduced training and supervision requirements, and a less specialised therapist profile—all of which are expected to result in lower overall costs. A recent multicentre open cohort study based on routine outcome monitoring (ROM) demonstrated the feasibility of GIT-PD and suggested effect sizes comparable to those of most specialist treatments for PDs [32]. Lacking a control group and randomisation, the extent to which these findings are subject to bias and confounding remains unclear, warranting confirmation in a randomised controlled trial.

A limitation of the current evidence base surrounding treatments for PDs is its predominant reliance on average treatment effects. All the while, these average effects face substantial heterogeneity [10, 11, 13, 14, 33, 34], meaning that individual treatment responses vary greatly. As specialist treatments have failed to demonstrate superiority over generalist models at the group level, it has been suggested that differences between the two might be spurious, but specific subgroups of patients might benefit from specialist treatment [11, 25]. Therefore, personalised treatment selection is seen as a potentially favourable approach to optimise treatment response and resource allocation [33, 34] in which patient characteristics inform the selection of the most appropriate treatment [35, 36]. To date, research has sought to discern characteristics which can predict treatment response and has tentatively suggested some (for instance, psychiatric symptom severity [37], younger age, treatment motivation and expectations, external barriers to treatment access (e.g. work engagements [38]), personality functioning [39], comorbid PD traits [40], and mentalizing capacity [41]), but reliable, meaningful, or consistently reproducible moderators remained unidentified. This is not surprising, as most efforts have focused on single or multiple variables each in isolation [42]. Furthermore, several studies have demonstrated that incorporating multiple patient characteristics into a model simultaneously yields more accurate and robust predictions of differential treatment response than relying on a single variable [36, 43]. One promising specific statistical method enabling personalised treatment selection is the Personalised Advantage Index (PAI), introduced by DeRubeis et al. [44]. This algorithm identifies and combines multiple treatment moderators to generate individualised treatment recommendations.

The utility of the PAI in matching patients to their optimal treatment has been supported by several secondary analyses of RCTs [36]. For example, Keefe et al. [45], in a reanalysis of the McMain et al. [29] RCT comparing DBT and GPM for individuals with BPD, found that patients with high psychiatric symptom severity and impulsivity derived greater benefit from GPM. All the while, those reporting higher levels of dependency, greater psychosocial impairment, and a history of childhood emotional abuse benefited more from DBT. The five identified predictors each independently interacted with treatment, significantly predicting treatment outcome and remaining significant when combined in one omnibus model. Overall, Keefe et al. [45] found that participants who received their PAI-predicted optimal treatment experienced significantly better outcomes than those who received their non-optimal treatment, especially when the prediction was relatively stronger with a medium-to-large effect size. Meanwhile, no *single* variable was a large-effect predictor of differential treatment response. These findings suggest that identifying and combining patient characteristics that predict differential treatment response could support a more personalised treatment allocation and improvement of treatment response, consequently facilitating the optimal use of limited specialist resources.

Another important consideration is the continued reliance on traditional categorical models of PDs of almost all studies, despite the introduction of dimensional approaches in Section III of the Diagnostic and Statistical Manual of Mental Disorders (5th ed.) [46], and more recently, the adoption of a dimensional conceptualisation of PDs in the International Classification of Diseases (11th ed.) [47]. The core shift from categorical to dimensional models is a transition from a typological framework (e.g. borderline PD, antisocial PD) to one that primarily distinguishes personality disorders based on severity levels (moderate, severe, extreme PD). As the evidence supporting the clinical utility of the AMPD solidifies [48–51], there is an urgent need for studies that evaluate treatment outcomes across subgroups defined by severity of personality functioning, and studies that assess treatment efficacy using dimensional constructs of personality pathology [52, 53].

The main objective of the present study (P-DAET) is to demonstrate the non-inferiority of a generalist treatment (GIT-PD) compared to two widely implemented specialist treatments in regular clinical practice in the Netherlands—MBT and ST—in patients with severe personality disorder, as defined by the dimensional framework of the Alternative Model for Personality Disorders (AMPD). Additionally, the study will apply the PAI to explore optimal treatment allocation across both generalist and specialist treatment conditions and address direct and long-term cost differences between conditions. By combining a dimensional diagnostic framework with a personalised treatment allocation approach, this study aims to contribute to more optimally allocated, effective, and scalable interventions for individuals with severe personality disorders, ultimately supporting better clinical outcomes and more efficient use of scarce mental health resources.

### Explanation for choice of comparator {9b}

Specialist psychotherapies are currently recommended in national and international guidelines as first-choice treatment for adults with severe PD, more specifically referring to DBT, MBT, ST, and TFP [9]. Given their availability in the participating institutions, MBT and ST are included in the comparator condition. Importantly, the aim of this study lies not in comparing specific methods (e.g. GIT-PD versus MBT or GIT-PD versus ST), but in comparing generalist versus specialist approaches (e.g. GIT-PD versus MBT and ST) that adhere to predefined required conditions of implementation. These are outlined under Intervention description {15a}.

### Objectives {10}

#### Primary objective

The primary objective is to determine whether generalist treatment (GIT-PD) is non-inferior (*d* ≥ − 0.25) to specialist treatment (MBT/ST) in improving personality functioning in participants with severe personality disorders from baseline to the end of treatment (18 months; T4). In setting the non-inferiority margin, scarce evidence is available on the difference between the selected specialist treatments (MBT/ST) and no treatment [14]. However, Cristea et al. [10] demonstrated that psychotherapy is between *d =* 0.25 and *d =* 0.56 more effective than treatment-as-usual in improving BPD-relevant outcomes. Therefore, taking the statistically conservative route, the non-inferiority margin is set at *d =* − 0.25, implying that non-inferiority will be concluded if the lower bound of the confidence interval for the effect of generalist treatment relative to specialist treatment in improving personality functioning at T4 is greater than − 0.25 (Cohen’s *d*).

#### Secondary objectives

The secondary objectives are, first, to assess whether generalist treatment (GIT-PD) is non-inferior (*d* ≥ − 0.25) to specialist treatment (MBT/ST) in improving general symptom severity and psychosocial functioning in participants with severe personality disorders from baseline to the end of treatment (18 months; T4). Second, to evaluate whether generalist treatment (GIT-PD) is non-inferior to specialist treatment (MBT/ST) in participants with severe personality disorders in maintaining improvements observed at 18 months in personality functioning, general symptom severity, and psychosocial functioning from baseline to 12-month follow-up (30 months; T6). Third, to determine whether generalist treatment (GIT-PD) is more cost-effective than specialist treatment (MBT/ST) in terms of improvements in personality functioning for participants with severe personality disorders. Fourth, to explore the extent to which an algorithmically optimised combination of demographic, clinical, and psychosocial variables can predict differential treatment response (as measured by change in level of personality functioning (LPF) between baseline and end of treatment) between generalist (GIT-PD) and specialist (MBT/ST) treatments, with the expectation that combining predictors in one algorithm will outperform chance-level prediction.

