The secondary outcomes, among others, include the mean differences in change from baseline to the end of treatment (T4) in symptom severity (SIPP-SF, SCID-5-PQ, BSI, C-SSRS; for an outline of the here-abbreviated outcome measures, see *Plans for assessment and collection of trial data {25a})* and psychosocial functioning (WHODAS 2.0, EQ-5D-5 L, Q-LES-Q-SF) between the generalist (GIT-PD) and specialist treatment (MBT/ST) conditions. Additional secondary outcomes assess the mean differences in change from baseline to follow-up (T6) between the generalist (GIT-PD) and specialist treatment (MBT/ST) conditions in personality functioning (STiP-5.1, LPFS-BF 2.0), symptom severity (SIPP-SF, SCID-5-PQ, BSI, C-SSRS), and psychosocial functioning (WHODAS 2.0, EQ-5D-5 L, Q-LES-Q-SF). For both the short- and long-term outcomes, all available measurement points are included in the model. The secondary outcome surrounding cost-effectiveness and cost-utility of generalist (GIT-PD) versus specialist treatment (MBT/ST) addresses the incremental effects set off against the incremental costs from baseline to end of treatment (T4), calculating an incremental cost-effectiveness ratio (ICER). For the cost-effectiveness analysis, improvement in personality functioning (STiP-5.1, LPFS-BF 2.0) is set off against the incremental costs, referring to direct and indirect costs, such as treatment costs (electronic patient file data), further healthcare consumption and productivity loss (TiC-P). All the while, cost-utility is measured in quality-adjusted life years (QALYs) gained throughout the assigned intervention, calculated from EQ-5D-5L scores. The final secondary outcome measures the combined predictive value of end-of-treatment differential treatment response, based on several pre-randomisation variables. The predictive value is expressed in a personal advantage score in terms of LPF improvement from baseline (STiP-5.1, LPFS-BF 2.0). The pre-randomisation variables with prescriptive and/or prognostic value are selected and used for predicting advantage scores through the development of a PAI algorithm. For a detailed description of the instruments and the timeline of assessment, see *Plans for assessment and collection of outcomes {25a}* and *Participant timeline {18}*.

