
To answer the secondary research questions regarding long-term (T6; 30 months) non-inferiority of generalist (GIT-PD) versus specialist treatment (MBT/ST) in improving personality functioning, an identical intention-to-treat longitudinal multilevel model will be fit as for the primary outcome, while including all available repeated measures. This ultimately results in the inclusion of three and seven repeated measures for the STiP-5.1 and LPFS-BF 2.0, respectively. Likewise, to assess the short-term (T4; 18 months), as well as the long-term (T6; 30 months) non-inferiority of generalist (GIT-PD) versus specialist treatment (MBT/ST) in improving symptom severity and psychosocial functioning, the same intention-to-treat longitudinal multilevel model will be applied for each of the secondary study parameters (SIPP-SF, SCID-5-PQ, BSI, C-SSRS, WHODAS 2.0, EQ-5D-5 L, Q-LES-Q-SF). Likewise, for the short-term outcome, the five repeated measures (level 1) of each individual (level 2) are nested within treatment sites (level 3). Models are adjusted for the respective outcome’s baseline value, random intercepts, and slopes are modelled at the second and third level to account for heterogeneous individual and treatment site change trajectories over time, and two-tailed significance levels are set at *α* = 0.05, while effect estimates are reported with corresponding 95% two-sided confidence intervals. The non-inferiority margin is set at *d* = − 0.25. On top of that, all AEs and SAEs are descriptively reported for both treatment arms.

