## Discussion

Although generalist treatments are widely used, the P-DAET trial is the first RCT assessing the non-inferiority of generalist treatment (GIT-PD) compared to specialist treatment (ST/MBT). We expect to find that, on average, generalist treatment is non-inferior to specialist treatment in terms of improving the level of personality functioning, general symptom severity and psychosocial functioning at post-treatment (18 months), as well as maintaining improvements at follow-up (30 months). Additionally, generalist treatment is expected to be more cost-effective than specialist treatment at both post-treatment and follow-up. Lastly, it is hypothesised that a combination of individual participant characteristics can predict differential treatment response above chance level, enabling the construction of a personalised treatment selection algorithm. P-DAET is, ultimately, aiming to contribute to the organisation of accessible and optimal allocation of cost-effective evidence-based psychotherapeutic care for those suffering from severe personality disorders by addressing these gaps in our current knowledge. The core clinical relevance of this study is determining whether a well-structured generalist treatment can serve as a non-inferior alternative to specialist treatment on average, while identifying which patients in particular require specialist care.

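### The 30-month objective and expected conclusion speak of maintaining 18-month gains, but the planned T6 test measures change from baseline and cannot show maintenance

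*Protocol article*

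**What the plan says.** - **Objectives {10}, Secondary objectives.** The first secondary objective concerns improvement up to T4. The second uses a different verb: non-inferiority in "maintaining improvements observed at 18 months in personality functioning, general symptom severity, and psychosocial functioning from baseline to 12-month follow-up". The sentence therefore names both the 18-month state and baseline as its reference.
- **Outcomes {16}.** The matching outcome refers to baseline only: "Additional secondary outcomes assess the mean differences in change from baseline to follow-up (T6) between the generalist (GIT-PD) and specialist treatment (MBT/ST) conditions".
- **Statistical methods {27a}.** The long-term question is put as one of improving. For personality functioning, "an identical intention-to-treat longitudinal multilevel model will be fit as for the primary outcome, while including all available repeated measures", which leads to the "inclusion of three and seven repeated measures for the STiP-5.1 and LPFS-BF 2.0, respectively". The symptom and psychosocial outcomes get the same model. "Models are adjusted for the respective outcome’s baseline value", and the margin is d = −0.25.
- **Discussion.** The authors expect non-inferiority at post-treatment, "as well as maintaining improvements at follow-up (30 months").

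The article defines no change from T4 to T6, no criterion for retained gain and no within-arm durability estimate. Section {27d} plans nothing beyond the analyses already described. The Discussion says the 24- and 30-month visits allow later or lasting effects to be examined, but names no analysis for this.

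**The concern.** The objective and the expected conclusion are about keeping a gain. The statistic is about the total change since baseline. The two answer the same comparative question only if the arms are level at T4, and even then a between-arm difference does not say whether either arm kept anything.

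Durability is a central question for a generalist treatment expected to be delivered at a lower dose, and the last two visits are there to examine it. As worded, a T6 result within the margin would be reported as non-inferior maintenance when the number behind it does not measure maintenance.

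**Working it through.** **Inputs.** From Sample size {19}: 158 evaluable per group, correlation 0.50 between repeated measures, two-sided 95% interval, margin 0.25 SD, 0.30 SD change in each arm. No attrition figure is given for T6, so 158 per group at T6 is an assumption. SD is set to 1, with equal correlations.

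**The plan's own figure.** For a linear treatment-by-time contrast over seven equally spaced measures, the variance per subject is 0.5/(28/36) = 0.643. Then n = 2 × 0.643 × (1.960 + 0.842)² / 0.25² ≈ 162 per group, or 324 in total against 316 stated (2.5% apart). With the actual visit times the total is 302. The inflation is exact: 316/0.883 = 357.87, so 358. The inputs are therefore a fair basis for what follows.

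**What the T6 statistic contains.** Write D for generalist minus specialist improvement. Then D(T0–T6) = D(T0–T4) + D(T4–T6). The plan tests the left side. Maintenance is the last term.

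**Standard errors at 158 per group**
- Change score (T0–T6 or T4–T6): √(2/158 × 2 × 0.5) = 0.1125
- T6 adjusted for baseline (ANCOVA): √(2/158 × 0.75) = 0.0974

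**Probability of concluding non-inferiority:** Φ((D + 0.25)/SE − 1.96). For D = 0: change score Φ(2.222 − 1.96) = 0.60; ANCOVA Φ(2.566 − 1.96) = 0.73.

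| Improvement at T4 → T6 (SD) | D(T0–T6) | Planned contrast (change score / ANCOVA) | D(T4–T6) | T4–T6 contrast |
|---|---|---|---|---|
| Both 0.30 → 0.30 | 0 | 0.60 / 0.73 | 0 | 0.60 |
| Both 0.30 → 0 | 0 | 0.60 / 0.73 | 0 | 0.60 |
| Specialist 0.30 → 0, generalist keeps 0.30 | +0.30 | about 1.00 | +0.30 | about 1.00 |
| Generalist 0.60 → 0.30, specialist keeps 0.30 | 0 | 0.60 / 0.73 | −0.30 | 0.008 |
| Generalist 0.30 → 0.15, specialist keeps 0.30 | −0.15 | 0.14 / 0.18 | −0.15 | 0.14 |
| Generalist 0.30 → 0, specialist keeps 0.30 | −0.30 | 0.008 / 0.007 | −0.30 | 0.008 |

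The 0.60 gain in the fourth row is illustrative. A simulation of 4,000 trials per row agrees; for ANCOVA it gives 0.72 when both arms keep their gain and 0.73 when both lose it. Under the seven-measure slope model the first two rows both become 0.79, so they still cannot be told apart.

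**Reading the table.** Rows 1 and 2 are the same to the planned test. In row 4 an early generalist lead hides a loss that exceeds the margin. In row 3 the comparative conclusion is true, but the comparator has lost its gain. In rows 5 and 6 the arms are level at T4, so the planned test and a T4–T6 test have the same target and behave alike.

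**The case against.** Several counter-arguments have force.

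- **The objective's own sentence refers to baseline.** It is comparative and does not promise maintenance in each arm, and Outcomes and {27a} apply the baseline reference consistently. This stands. The fault is one of mixed wording, and rewording removes much of it.
- **Equal relapse defeats any between-arm non-inferiority test, including one on T4–T6 change.** This stands: row 2 gives 0.60 for that contrast too. Within-arm estimates are therefore part of the fix.
- **T4 and T6 estimates will both be reported, so a shrinking lead would be visible.** This stands in part. Subtracting two estimates from separate models gives a rough value without a confidence interval, and says nothing about change within an arm.
- **T4 may not be the same treatment phase in both arms.** The Discussion allows low-intensity booster sessions after 18 months. This stands as a limit on interpreting T4–T6 change.
- **Section {27d} covers extra subgroup and sensitivity analyses and does not bar further contrasts.** That is fair. The point rests on the mismatch between the stated objective and the stated outcome, not on that section.

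Two stronger readings are tempting. A reader might infer that maintenance could be declared after either arm alone had lost its gain. Row 6 shows otherwise: a generalist-only loss of an equal 0.30 SD gain passes in under 1% of trials. A reader might also infer that any larger generalist loss which passes is a false conclusion. If specialist stays at 0.50 and generalist falls from 0.60 to 0.40, D(T4–T6) = −0.20, which lies inside −0.25. Passing there, in about 27 to 34% of trials, would be correct.

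**Conclusion.** The point holds in a limited form. The second secondary objective and the Discussion speak of maintained 18-month gains, while the planned outcome and model test change from baseline to T6. That statistic gives the same chance of a non-inferiority conclusion (0.60 to 0.73) whether both arms keep or lose everything gained by T4.

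The problem is confined to three situations: equal loss in both arms, loss in the specialist arm, or a generalist arm ahead at T4. The primary analysis and the sample size are untouched. The figures assume unit SD, equal correlations of 0.50 and 158 per arm still observed at T6; further attrition would lower the probabilities at D = 0.

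The documents do not support asking for a new formal non-inferiority test on T4–T6 change with within-arm conditions. The objective is comparative, and that test would have power of only about 0.60 under equal maintenance.

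**What to change.** 1. In the Secondary objectives and the Discussion, word the T6 result as *non-inferior in improvement from baseline to 30 months*.
2. In Outcomes {16} and Statistical methods {27a}, add two sets of estimates from the T6 model already planned: the between-arm difference in T4-to-T6 change, and each arm's own T4-to-T6 change, all with 95% confidence intervals. The model must let T4 and T6 have their own means; a single straight line over time would fix this change in advance.
3. Base any statement about maintenance on these estimates. No further formal test or within-arm threshold is needed.

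**Cost.** A few extra contrasts per outcome and no new data, since T4 and T6 are already in the model. The T4–T6 contrast is somewhat less precise (SE about 0.11 against 0.10 SD for the baseline-adjusted T6 difference), and its interpretation should mention possible booster treatment after T4.
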